### Economic evaluation

In accordance with the primary aim of the clinical trial, the primary outcome for the economic evaluation will be the number of women with satisfactory results, i.e., subjectively improved, at 6, 12 and 18 months. During the period that women allocated to PFMT follow their training program, women whom underwent TVT(O) may already experience a period with satisfactory outcome. This time aspect will be accounted for by estimating and comparing person time with satisfactory results.

Health related quality of life (HRQoL) is considered a important outcome. In addition to the disease specific questionnaires (UDI and IIQ), two global questions, Patient Global Impression of Severity and Patient Global Impression of Improvement, (PGI-S and PGI-I), and a generic questionnaire, Euroqol 5D (EQ-5D) will be filled out at baseline and at regular intervals up to twelve months after completion of treatment. Using the EQ5D the outcome in terms of quality adjusted life years (QALYs) can be estimated. The effects observed by means of the disease specific questionnaire will be reported separately. [16-18]

Costs of the strategies directly TVT(O) as well as PFMT will be estimated using a societal perspective. Accordingly, direct medical costs will be based on the actual costs of the personnel and other resources used such as incontinence pads. Unit costs will be based on a specific costing study conducted in the hospital setting and the primary care setting. Where available unit costs will be based on the standard prices published in the current guidelines. Also, as PFMT is much more time consuming for the patients the costs associated to sick leave at work will be estimated using the friction cost method. The hours women spend on travel and training etc. will be assessed by questionnaires and subsequently valued.

#### COST-EFFECTIVENESS

The incremental costs per QALY gained will be estimated at one year. Uncertainty will be evaluated using standard bootstrap techniques (1,000 replicates). The incremental costs and effects will be depicted in a cost-effectiveness analysis (CEA) plane. The resulting 'scatter plot' provides information directly interpretable as the probability of one intervention being cost-effective compared to the alternative.

### Statistical analysis

Data will be presented as numbers (percentage) for nominal variables or means (standard deviation) for interval variables. Differences between the two interventions will be analysed based on intention-to-treat analysis. For interval variables, differences between the two groups will be analysed with a Students t-test, proportions will be compared using the Chi-square test.

Multivariate logistic regression analysis will be used for the development of the prediction of successful treatment only. In literature, a wide range of patient characteristics were considered to be associated with the outcome of PFMT. In the Consultation on Incontinence (ICI) proceedings it was concluded that there are no reliable factors identified yet, because the number of observations and studies is too low.[2] However, several factors have been identified as possible predictors of a successful outcome after PFMT. To provide information on treatment effectiveness in different subgroups of patients participating in this trial, we will derive a prediction model and estimate interaction of treatment effect with baseline incontinence severity (number of leaks/week), duration of symptoms, increasing parity, Body Mass Index, baseline pelvic floor contraction ability, and treatment modality as factors.[2] The defined prediction model will therefore be pre-specified resulting in less over-optimism than models in which the choice of predictors is strongly driven by the data-set and the need for external validation.[19] From the multivariate logistic model, in which success will be defined as cure (no objective or subjective incontinence) at 12 and 18 months follow-up, we will estimate the weight of the different coefficients. The modelling process will be internally validated by bootstrap resampling. This technique gives an impression of how "over-optimistic" the model is i.e., how much the performance of the model may deteriorate when applied to a new group of similar patients.[20]

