### Study design and setting

The PORTRET study is a multidisciplinary, multicentre non-blinded therapeutic randomised controlled trial. Randomisation will be performed centrally with computerised randomisation tables. The two trial arms are PFMT by a specialised physiotherapist and a surgical intervention with the TVT or TVT-O. Recent data show that both the TVT and TVT-O are equally effective.[12,13] For obvious reasons blinding of treatment between PFMT and surgery will not be possible. To reflect daily practice as close as possible the assessment of costs will start directly after randomisation. We expect that the maximum effect of PFMT will be reached within 3-6 months. To account for possible changes in symptoms and changes in costs during this period, cost and symptom assessments are made every two months by means of a telephone administered questionnaire during the first 4 months. After that an assessment at 6, 12 and 18 months is performed. From literature, one of the predictive factors for the efficacy of treatment is the severity of incontinence at baseline. Therefore, we will introduce stratification by severity into the randomisation. We will stratify according to the severity (moderate or severe) as established by the Sandvik index [see table 1]. [14] The flowchart and study design are presented in figure 1 and table 2

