### Patient follow-up procedures

Patients will be followed from the start of primary therapy until 18 months later. Follow up will consist of various elements

In all patients the next items will be recorded at inclusion:

1. Baseline characteristics

2. History and clinical examination

3. 48 h-bladder (voiding and incontinence) diary

4. 24 h-padtest

5. Validated Quality of Life questionnaires (Urinary Distress Inventory, Incontinence Impact Questionnaire, Euroqol 5D, patient global impression of severity/improvement)

6. Uroflow measurement including post void residual volume

7. Cost-analysis questionnaire

The onset of primary therapy, either TVT(O) in the surgery arm of the study or PFMT in the physiotherapy arm of the study will be T = 0

In case of surgery, the patient will receive the standard care associated with the pre-, per- and postoperative standards of the participating hospital. She will visit the hospital after surgery at 6 weeks, 6, 12 and 18 months. Questionnaires will be handed out at these visits containing the items mentioned above. Furthermore, special attention will be given with respect to extra visits to the general practioner, physiotherapist or specialist visits in relation to the surgical procedure that might have taken place and physical examination will be performed. Costs associated with incontinence and therapy will also be assessed with telephone administered questionnaire at 2 and 4 months follow-up. Women who are enrolled for PFMT will be followed-up according to the same schedule besides the 6 weeks post operative check-up.

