### Patient outcome measures

This study will compare the clinical and cost-effectiveness of PFMT versus the TVT/TVT-O procedure as treatment for moderate to severe stress urinary incontinence.

Primary outcome: Subjective improvement of urinary incontinence

Secondary outcome(s):

1. Complete cure on objective and subjective parameters.

2. Subjective improvement in generic and disease-specific quality of life.

3. Complications and de novo urogenital symptoms.

4. The incremental cost-effectiveness of TVT as compared to PFMT, accounting for direct and indirect costs parameters.

5. Development of a prediction model for successful treatment, with the therapy given (PFMT or TVT) as independent variable in the model.

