### Sample size considerations

Literature shows a subjective improvement of incontinence after PFMT up to 65%, and a subjective improvement after TVT(O) of at least 80%. In order to detect this difference with a power of 0.9 and an alpha of 0.05, we need 200 women in each trial arm. For our primary outcome parameter, total cure of incontinence, the expected difference between both arms is much larger: 28% cure after PFMT, and 65% cure after TVT. The 200 women in each treatment arm will be largely sufficient to assess a statistically significant difference in this secondary outcome.

Sample size calculation for the prediction models is based on the number of successes (or failures). For each predictor in the model we need 10-15 successes. Our pre-defined prediction model consists of 5 predictors and the interaction terms with treatment. Our total sample size will exist of 400 women. The expected number of successes (cure) of the PFMT group is 30 (15% of 200) women, the number of women cured after TVT is an estimated 130 (65% of 200 women). So the total number of complete cure is an estimated 160 women, with 240 women being not completely cured. These figures are sufficient for modelling up to 10-12 predefined possible predictors of cure. With respect to subjective improvement an estimated total of 290 women will show subjective improvement as measured with the Patient Global Impression of Improvement (PGI-I) questionnaire (65% of 200 women with PFMT plus 80% of 200 women in TVT group). Thus, 110 women can be considered failures. Again, this also allows us to make a prediction model for improvement with the predefined predictors. Therefore the study sample will also be amply sufficient for prediction purposes.

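### The covariate-free t-test for UDI, IIQ and EQ-5D is valid, but it gives up precision that baseline scores already collected would supply

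*Protocol article*

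**What the plan says.** The Statistical analysis section names the test for scale outcomes: "For interval variables, differences between the two groups will be analysed with a Students t-test". Proportions go to a chi-square test, and both comparisons are by intention to treat. Regression is confined to another purpose: "Multivariate logistic regression analysis will be used for the development of the prediction of successful treatment only". No baseline value or stratification factor enters any comparison of the two arms.

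The baseline data exist. Patient follow-up procedures lists "Validated Quality of Life questionnaires" among the items recorded at inclusion, covering UDI, IIQ, EQ-5D and the global impression items. Table 2 shows UDI and IIQ at the baseline visit and at 6, 12 and 18 months. It shows EQ-5D at study entry and at the same three follow-up visits. Economic evaluation says that these instruments "will be filled out at baseline and at regular intervals up to twelve months after completion of treatment".

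The secondary outcome is worded as "Subjective improvement in generic and disease-specific quality of life". The text does not say whether the t-test is to be run on follow-up scores or on change from baseline.

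Study design and setting states that "one of the predictive factors for the efficacy of treatment is the severity of incontinence at baseline", and stratifies the randomisation on it (moderate or severe by the Sandvik index).

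**The concern.** A two-sample t-test leaves in its error term the part of the between-woman variation that the baseline score could explain. It also makes no correction for a chance difference between the arms at baseline. The protocol itself regards baseline severity as prognostic and balances the arms on it, yet the named analysis does not use it. At stake is the width of the confidence intervals for UDI, IIQ and EQ-5D, and so the power to show a quality-of-life difference.

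A related question concerns the cost-effectiveness result. Baseline utility is part of a one-year QALY computed as an area under the curve, so a chance baseline gap in EQ-5D carries into the incremental QALY unless it is adjusted for.

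**Working it through.** **The plan's own figure.** The document gives no calculation for an interval outcome. Its one sample size is for subjective improvement: 65% against 80%, power 0.9, alpha 0.05 (taken as two-sided), 200 per arm. The pooled normal formula is n = [z₀.₉₇₅√(2p̄q̄) + z₀.₉√(p₁q₁ + p₂q₂)]²/δ², with p̄ = 0.725 and δ = 0.15. It gives 185 per arm, and 198 with the continuity correction, so 200 is reproduced. Nothing below changes it.

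**Inputs for the scale outcomes.** n = 200 per arm is from Sample size considerations. The correlation r between baseline and follow-up score is assumed to be 0.3, 0.5 or 0.7. Variances at baseline and follow-up are assumed equal, with a common slope in both arms.

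**Variance of the treatment difference, relative to a follow-up-score t-test (= 1).**

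- Change-score t-test: 2(1 − r)
- ANCOVA: 1 − r²
- ANCOVA relative to change score: (1 − r²)/[2(1 − r)] = (1 + r)/2

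| r | Change-score t-test | ANCOVA | ANCOVA saving vs follow-up score | ANCOVA / change score | ANCOVA saving vs change score |
|---|---|---|---|---|---|
| 0.3 | 1.40 | 0.91 | 9% | 0.65 | 35% |
| 0.5 | 1.00 | 0.75 | 25% | 0.75 | 25% |
| 0.7 | 0.60 | 0.51 | 49% | 0.85 | 15% |

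**In women per arm.** ANCOVA on 200 per arm is worth a follow-up-score t-test on 200/0.91, 200/0.75 or 200/0.51, about 220, 267 or 392. It is worth a change-score t-test on 200/0.65, 200/0.75 or 200/0.85, about 308, 267 or 235.

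**In detectable difference.** At 80% power a follow-up-score t-test detects (1.960 + 0.842) × √(2/200) = 0.280 SD. Multiplying by √(1 − r²), ANCOVA detects 0.267, 0.243 or 0.200 SD. At a true difference of 0.280 SD, power rises from 80.0% to 83.6%, 89.9% or 97.5%.

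**QALY.** Under Cost-effectiveness the QALY horizon is one year. Table 2 gives EQ-5D at entry, 6 and 12 months, so the trapezium rule has weights 0.25, 0.50 and 0.25. With equal variances, a chance baseline gap g is expected to persist as r × g at each later visit. The expected shift is therefore g(0.25 + 0.75r). For an illustrative g = 0.02:

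- r = 0.3: 0.02 × 0.475 = 0.0095
- r = 0.5: 0.02 × 0.625 = 0.0125
- r = 0.7: 0.02 × 0.775 = 0.0155
- gap persisting in full: 0.02 × 1 = 0.02

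**The case against.** The strongest reply is that the protocol names a test but not the variable it is applied to. Because the outcome is worded as improvement, a t-test on change from baseline is a fair reading, and that test does use the baseline. This stands. A reader might infer that the baseline is ignored, or that the loss reaches 49%; both hold only if follow-up scores are meant. Against change scores the saving falls as r rises, from 35% to 15%. There is still a saving under either reading.

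It can also be said that r is nowhere in the document. That is so. If r is low, which is possible when many women are expected to be cured, the gain over a follow-up-score t-test is small: 4% at r = 0.2.

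A reader might go further and infer that the t-test is biased, or that the main result is in doubt. Neither follows. Under randomisation the t-test is unbiased and its interval already allows for chance imbalance. The primary outcome is a proportion.

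Nor does the point reach every secondary outcome. Cure and complications are proportions. The bladder diary and pad test are not listed as interval outcomes, and Table 2 has neither at 18 months (the pad test is repeated only at 12). Table 2 shows no pre-treatment cost measure.

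The QALY part does not follow from the t-test sentence. Cost-effectiveness specifies a bootstrap with 1,000 replicates and is silent on adjustment, which may properly be settled in a separate plan. It is a recommendation, not an error in the text.

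An analysis plan not shown here might specify ANCOVA. It would then depart from a method that this document states, so the wording still needs changing.

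**Conclusion.** The point holds as a matter of efficiency on the secondary quality-of-life scales. The stated t-test is valid but less precise than a baseline-adjusted analysis on either reading of improvement. For assumed r = 0.3, 0.5 and 0.7, the variance saving is 9%, 25% and 49% against follow-up scores, or 35%, 25% and 15% against change scores. The change-score figures also assume equal baseline and follow-up variances. Any further gain from the Sandvik stratum cannot be computed from the document.

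For the one-year QALY difference, a chance baseline gap of 0.02 would be expected to shift the result by about 0.010 to 0.016 for r = 0.3 to 0.7. The full 0.02 is a ceiling, reached only if the gap does not shrink at all. No conclusion of the trial is shown to be wrong.

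**What to change.** For UDI, IIQ and EQ-5D, replace the t-test by ANCOVA at each visit: linear regression on treatment, baseline value and Sandvik stratum. A single mixed model over 6, 12 and 18 months with the same covariates would also serve. State that the estimate is the adjusted mean difference with its confidence interval, which also removes the ambiguity between follow-up and change scores.

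As a secondary step, adjust the one-year QALY difference for baseline EQ-5D within each bootstrap replicate. Before EQ-5D is used as a covariate in either analysis, reconcile Table 2, which places it at study entry in a column after randomisation, with Patient follow-up procedures, which places it at inclusion. In an unblinded trial a baseline value given after allocation is known could itself be affected by it.

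The cost is a change of wording before analysis and slightly more analysis work. It needs no new data and no more women.

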**Figure 2 F2:**
[figure not shown]
**Study inclusion and exclusion criteria**.

Randomisation will be performed with the use of computerised randomisation tables. The randomisation will be stratified according to the severity of incontinence (moderate or severe as established by the Sandvik index. For obvious reasons (surgery versus conservative treatment) both the randomisation outcome and the personal involved in outcome assessment cannot be blinded.

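### Randomisation is stratified by Sandvik severity but the named test ignores the strata, so the planned comparison is mildly conservative if severity is prognostic; validity and planned power are not at risk

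*Protocol article*

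**What the plan says.** Under Study design and setting, the protocol article gives its reason for stratifying: "one of the predictive factors for the efficacy of treatment is the severity of incontinence at baseline". The Randomisation section repeats the design feature: "The randomisation will be stratified according to the severity of incontinence", with two levels, moderate and severe, on the Sandvik index.

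Under Patient outcome measures, the main endpoint is given as "Primary outcome: Subjective improvement of urinary incontinence". The Sample size considerations treat it as a proportion: "Literature shows a subjective improvement of incontinence after PFMT up to 65%, and a subjective improvement after TVT(O) of at least 80"% (the percent sign falls outside the quoted run).

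For the between-arm comparison, the Statistical analysis section states intention-to-treat and then that "proportions will be compared using the Chi-square test". The next paragraph confines regression to another purpose: "Multivariate logistic regression analysis will be used for the development of the prediction of successful treatment only". No section describes a stratified or severity-adjusted treatment comparison.

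**The concern.** Stratified randomisation with balance inside each stratum removes the between-stratum part of the outcome variation from the difference between arms. The plain chi-square test estimates its variance from the pooled proportion, which still contains that part. If the stratifier is prognostic, which is the protocol's own reason for using it, the estimated standard error exceeds the true one. The test then rejects a true null less often than 5%, and some of the precision bought by the design is not used.

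What is at stake is efficiency and consistency between design and analysis. The article names the test and limits the role of regression, so this is a stated choice and not mere silence. Settling the matter in advance also removes a later choice between adjusted and unadjusted results.

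**Working it through.** **Inputs from the protocol article.** Improvement 65% (PFMT) and 80% (TVT(O)), power 0.9, alpha 0.05, 200 per arm (Sample size considerations); two severity strata (Study design and setting; Randomisation).

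**Assumptions, because the article does not give them.** Two-sided alpha, all 200 per arm analysable, arms balanced within strata, the same 15-point treatment difference in both strata, half the women severe, and a moderate-severe gap *d* in improvement of 0 to 30 points.

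**Step 1: reproduce the planned size.** With p̄ = 0.725:

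n = [1.960·√(2·0.725·0.275) + 1.282·√(0.65·0.35 + 0.80·0.20)]² / 0.15² = 184.1, so 185 per arm.

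With continuity correction: (184.1/4)·[1 + √(1 + 4/(184.1·0.15))]² = 197.2, so 198 per arm. The stated 200 is reproduced to within rounding by an unstratified, continuity-corrected calculation. Power of the plain chi-square (uncorrected, severity ignored) at 200 per arm:

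Φ[(0.15·√200 − 1.960·√0.39875)/√0.3875] = Φ(1.42) = 92.2%.

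**Step 2: type I error.** Under the null at 72.5% in both arms, the pooled variance is 0.725·0.275 = 0.1994. With equal strata the between-stratum part is d²/4, so

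ratio = 1 − (d²/4)/0.1994, and type I error = 2·P(Z > 1.96/√ratio).

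| Gap *d* | Ratio | Type I error, formula | Type I error, simulated |
|---|---|---|---|
| 0 | 1.000 | 5.0% | 5.0% |
| 10 points | 0.987 | 4.9% | 4.9% |
| 20 points | 0.950 | 4.4% | 4.4% |
| 30 points | 0.887 | 3.7% | 3.8% |

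The simulation used 200,000 trials per scenario. The stratified Cochran-Mantel-Haenszel test stayed at about 5.0% throughout.

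**Step 3: standard error and power at 65% vs 80%.** Removing the between-stratum part gives variance 0.3875 − d²/2 in place of 0.3875. Chi-square power is Φ[(0.15·√200 − 1.960·√0.39875)/√(0.3875 − d²/2)]. For the stratified test, 0.39875 is also reduced by d²/2.

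| Gap *d* | Excess in unstratified SE, formula | Same, simulated | Power, chi-square vs stratified, formula | Same, simulated |
|---|---|---|---|---|
| 0 | 0% | 0.3% | 92.2% vs 92.2% | 92.3% vs 92.3% |
| 10 points | 0.6% | 0.9% | 92.4% vs 92.5% | 92.6% vs 92.8% |
| 20 points | 2.7% | 3.0% | 92.8% vs 93.4% | 92.9% vs 93.6% |
| 30 points | 6.4% | 6.7% | 93.5% vs 94.9% | 93.6% vs 95.0% |

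Before rounding, the power lost is 0.2, 0.7 and 1.4 points by formula (0.2, 0.7 and 1.5 in the simulation). Every entry is above 90%. Chi-square power itself rises with the gap, because stratified randomisation shrinks the true variance whichever test is used.

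**Step 4: sensitivity to the severe share.** At 30% severe and a 30-point gap, simulated power is 93.3% vs 94.6% and type I error 4.0%. At 70% severe and a 20-point gap, power is 92.7% vs 93.3% and type I error 4.5%. The picture does not change.

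**The case against.** The best answer is that almost nothing is lost. The test errs on the safe side, the sample size was worked out for an unstratified test, and the 90% target is exceeded in every scenario above. All of that stands, and it limits the point to efficiency and consistency.

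The size is also assumed and not found in the article. The protocol calls severity predictive without giving an effect. Its Statistical analysis section reports that no reliable predictors of PFMT outcome have yet been identified. The figures further need balance within strata, and the article describes stratified computerised tables without giving details of blocking. This stands too, which is why a range starting at zero is shown.

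Four stronger readings are tempting and are not supported:

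- **That the trial wastes up to 18% of its patients (73 of 400 women) or has a type I error of 3.3%.** That needs a 35-point gap. Combined with a common 15-point treatment difference and equal strata, it implies improvement of 97.5% in moderate women after TVT(O) and 47.5% in severe women after PFMT. Nothing in the article points to such values.
- **That the trial is underpowered or its test invalid.** The working shows neither. If, as an assumption, 15% were not analysable (170 per arm) and the gap were 25 points, simulated power would be 88.8% plain and 90.4% stratified. Most of that fall comes from the missing women, not from the choice of test.
- **That the word 'only' forbids a stratified test.** It restricts logistic regression. A Mantel-Haenszel analysis is not regression.
- **That severity is absent from the analysis.** Baseline leaks per week and their interaction with treatment are in the prediction model. That model targets cure, though, and does not supply the primary comparison.

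It may also be said that a condensed article leaves plain versus stratified testing to the full plan. That has some force, but the article does name a test and does limit regression. As written, the analysis does not use the strata.

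**Conclusion.** The inconsistency is real and its consequence is small. The protocol stratifies on a factor it considers related to outcome and then names a treatment comparison that leaves the factor out. With equal strata, within-stratum balance and gaps of 10 to 30 points, the plain chi-square has a type I error of about 4.9% to 3.8%. Its standard error is about 1% to 7% too large, and it gives up roughly 0.2 to 1.4 points of power at 200 per arm. With no severity effect the cost is zero.

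The article specifies no confidence interval for the treatment difference. The excess standard error would carry over to any interval computed the same unstratified way, making it slightly too wide. Validity is not threatened, and the planned 90% power holds with 200 analysable women per arm. The change is worth making because it is nearly free and aligns the analysis with the design.

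**What to change.** In the Statistical analysis section, make the primary comparison of subjective improvement, and the comparison of cure, a Mantel-Haenszel risk difference with 95% confidence interval and a Cochran-Mantel-Haenszel test. Stratify both by the severity stratum used at randomisation, and keep the plain chi-square as a sensitivity analysis.

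A logistic model with arm and stratum, reported as a standardised risk difference, is an acceptable alternative. Only in that case does the word 'only' in the sentence on regression need to go.

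The cost is a change of wording in the protocol or analysis plan, best made before outcome data are compared by arm. The stratum is already recorded, and neither the sample size nor data collection changes.

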**Figure 1 F1:**
[figure not shown]
**Flow chart**.

**Table 1 T1:** Sandvik Index

**SANDVIK INDEX**	Quantity of urine loss	
	
	1 = drops	2 = more than drops
Episodes		

1 = < 1 time a month	1	2

2 = 1 to more times a month	2	4

3 = 1 to more times a week	3	6

4 = daily	4	8

**Table 2 T2:** Study Design Schedule

	Baseline visit	Randomisation	study entry	2, 4 months*	6 months visit	12 months visit	18 months visit
Patient characteristics	X	**Checking Inclusion & Exclusion Criteria**					
		
**Gynaecologic examination**	**X**					**X**	
		
Assessment of pelvic floor functioning	X				X	X	
		
**48 hour bladder diary**	**X**				**X**	**X**	
		
Flow	X				X	X	
		
**Residual volume**	**X**				**X**	**X**	
		
Stress test	X				X	X	
		
**Sandvik index**	**X**				**X**	**X**	
		
24 hour pad test	X					X	
		
**Global Impression of severity**	**X**			**X**	**X**	**X**	**X**
		
Global Impression of improvement				X	X	X	X
		
**EQ-5D**			**X**		**X**	**X**	**X**
		
UDI	X				X	X	X
		
**IIQ**	**X**				**X**	**X**	**X**
		
Costs assessment*			X	X	X	X	X
		
**Compliance with treatment #**				**X**		**X**	
		
Complications of surgery#				X			

* After randomisation costs assessment will be made for both groups at 2 and 4 months in order to account for changes

occurring during progression of (PFMT) treatment.

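### The prediction model needs objective cure at 18 months, but Table 2 schedules no objective incontinence measure then and disagrees with the follow-up text

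*Protocol article*

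**What the plan says.** The Statistical analysis section of the protocol article fixes the outcome of the logistic prediction model: "success will be defined as cure (no objective or subjective incontinence) at 12 and 18 months follow-up". A woman therefore has to be free of incontinence on objective as well as subjective grounds, and 18 months is one of the two named time points. Patient outcome measures lists "Complete cure on objective and subjective parameters" as a secondary outcome without a time point.

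The assessment schedule is given twice. Table 2 (Study Design Schedule) has a column for an 18-month visit, but the rows for "24 hour pad test", "48 hour bladder diary", "Gynaecologic examination" and the stress test are blank there. Patient follow-up procedures says of a woman in the surgery arm: "She will visit the hospital after surgery at 6 weeks, 6, 12 and 18 months". It adds that questionnaires at these visits cover the items listed earlier in that section, a list that includes the diary and the pad test, and that a physical examination is done. PFMT women follow the same timetable apart from the 6-week check.

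On harms, "Complications and de novo urogenital symptoms" is a secondary outcome, also without a time point. Table 2 marks "Complications of surgery" only in the column for 2 and 4 months.

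**The concern.** A composite outcome can be scored only where all its components are measured. Under Table 2, the objective component exists at 12 months but not at 18. Cure at 18 months would then either be left unscored or rest on questionnaires alone. In the second case two different outcomes, the later one probably easier to meet, would carry the same name in a model whose stated protection against over-optimism is that it is pre-specified.

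The disagreement between table and text has a practical side as well. Recruitment runs across more than 30 hospitals. Sites working from Table 2 would collect no objective incontinence data at 18 months, while sites working from the text might collect some, so that missingness could differ by site. Tests not done at that visit cannot be recovered afterwards.

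**Working it through.** The question is one of schedule, so the check sets the passages side by side. Time points marked in Table 2:

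| Item | Baseline | 6 months | 12 months | 18 months |
|---|---|---|---|---|
| Stress test | yes | yes | yes | no |
| 48-hour diary | yes | yes | yes | no |
| Sandvik index | yes | yes | yes | no |
| 24-hour pad test | yes | no | yes | no |
| Gynaecological examination | yes | no | yes | no |
| Flow, residual volume | yes | yes | yes | no |
| UDI, IIQ | yes | yes | yes | yes |

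The 18-month column also holds PGI-S, PGI-I, EQ-5D and costs, and nothing else. The blanks do not look like a fault of text extraction, because the UDI, IIQ, EQ-5D and PGI rows fill the last column correctly.

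1. *At 12 months.* Stress test, diary and pad test are all marked, so composite cure can be scored.
2. *At 18 months under Table 2.* The number of objective incontinence measures marked is 0. Whether the model sentence means one outcome spanning both visits or two separate outcomes, it calls for an objective finding at 18 months that the table does not supply.
3. *At 18 months under Patient follow-up procedures.* There is a visit with a physical examination in both arms. The diary and pad test may come with it, because they are among the listed items; but the sentence speaks of questionnaires, and that list names no stress test. Table 2 leaves even the gynaecological examination blank at this visit.

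*Figures that do not move.* The sample size rests on subjective improvement of 65% against 80%, power 0.9 and alpha 0.05. With a two-sided test, the mean rate is (0.65 + 0.80)/2 = 0.725, and n = [1.960·√(2·0.725·0.275) + 1.282·√(0.65·0.35 + 0.80·0.20)]² / 0.15², which gives 185 per arm, or 198 with a continuity correction, against 200 stated. No input involves objective cure. The expected number of cures for the model also reproduces: 0.15·200 + 0.65·200 = 30 + 130 = 160, with no time point attached.

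*Complications.* The Table 2 row has one mark, in the column for 2 and 4 months. The follow-up text adds a 6-week visit after surgery and asks at the visits about extra consultations connected with the operation. UDI is marked at 6, 12 and 18 months, flow and residual volume at 6 and 12, and costs through 18. PFMT is planned over 6 months, so a woman who completes it and is then operated on passes the table's last complications mark before her operation. The footnote ties complications to surgery, not to the surgery arm.

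**The case against.** The strongest reply is that the follow-up text already provides what the model needs: an 18-month visit in both arms, a physical examination, and on one reading the diary and pad test. The Abstract adds that objective cure is judged from history and clinical parameters, and nothing in the article requires a stress test or pad test for that judgement. A journal article also condenses a fuller protocol and its case record forms.

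Much of this stands. A reader might infer from Table 2 that objective status at 18 months is missing by design for all 400 women, or that the outcome cannot be obtained. The documents do not support that, because the table is contradicted by the text and neither is declared to prevail. The reply does not remove the contradiction, however. The article does not say which clinical parameters count at 18 months, and its only itemised schedule shows none. This is a conflict within printed text, not detail left to another document.

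On complications, a reader might infer that recording covers only 4 of 18 months (22%), that later events go unrecorded, and that the harm of surgery is therefore understated. This does not follow. The outcome has no stated time point, early complications are recorded, and the later visits, UDI, flow, residual volume and cost items offer other routes by which later problems can appear. What remains is a table row that stops earlier than the text does.

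**Conclusion.** The point holds as an unreconciled conflict between Statistical analysis, Table 2 and Patient follow-up procedures. If Table 2 is followed, the objective half of 18-month cure is not collected, and any 18-month cure reported would differ in kind from 12-month cure. If the follow-up text is followed, some objective assessment may be available, but its content is not fixed.

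The reach is limited to the 18-month part of the secondary prediction model. Composite cure can be assessed at 12 months under either schedule. The primary outcome, measured with PGI-I, is marked at 2 and 4, 6, 12 and 18 months, and the sample size does not depend on any of this. The conclusion assumes that the printed columns of Table 2 are as the authors intended. The complications row is a minor inconsistency of the same kind, and no bias in the harm comparison has been shown.

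**What to change.** Reconcile the three places in one of two ways.

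- Define model success as objective plus subjective cure at 12 months, where stress test, diary and pad test are all scheduled, and report 18 months as subjective cure only. This costs a change of wording and gives up any objective statement at 18 months.
- If the 18-month visit in Patient follow-up procedures stands, mark the objective tests at 18 months in Table 2 and name those that define cure. This costs a little more testing at a visit already planned.

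For the minor point, add a complications item to Table 2 at the planned 6-, 12- and 18-month visits for every woman who has had a tape placed, in either arm. This costs one extra item on the case record form at visits that already exist.
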